#### Systemic reactions

Systemic reactions will be graded according to the Division of AIDS Table for Grading Severity of Adult and Pediatric Adverse Events (see Appendix 16.1). The investigational drug substance suppliers should be contacted within 24 hours for any systemic Grade 3 or 4 reactions thought definitely, possibly, or probably related to treatment. Further vaccines should not be given subject prior to consultation with the investigational drug suppliers.

# Treatment of Subjects

## Study drug and dosages

### Study drug description

#### Vacc-4x

The Investigational Medicinal Product (IMP), Vacc-4x, consists of four synthetic peptides (Vacc‑10 acetate, Vacc‑11 acetate, Vacc‑12 acetate, and Vacc‑13 acetate), each corresponding to conserved domains on the HIV-1 p24 capsid protein representing the native Gag regions with residues 166-185, 252‑269, 264-284, and 335-354, respectively.

Vacc-4x is manufactured by Bachem AG ([name]). Vacc-4x is manufactured in accordance with Good Manufacturing Practice (GMP). Vacc-4x is supplied as sterile vials of freeze-dried white powder. There is no additional ingredient in the product.

Vacc-4x should be mixed with Endocine and administered intranasal as a 150µl in each nostril.

#### Endocine

The Endocineadjuvant is a lipid based nano-emulsion consisting of mono-olein and oleic acid in a physiologically acceptable buffer. The nanoparticles have a size of less than 100 nm. The appearance of the nanoparticles is a white opalescent liquid with reological characteristics similar to water.

Endocine is manufactured by Galenica AB, Malmö, Sweden and is supplied in vials containing 250 µl of the adjuvant.

The final formulation to be administered contains the following ingredients:

| **Substances** | **Generic name** | **CAS number*** |
| --- | --- | --- |
| Mono-oleate | Glyceryl oleate | 97593-29-8 |
| Oleic acid | Oleic acid | 112-80-1 |
| NaOH | Sodium hydroxide | 95077-05-7 |
| Vacc-4 peptides |  | |
| Water | water |  |

* Chemical Abstracts Service. A division of American Chemical Society.

Due to instability of the Vacc-4x peptides, the final vaccine formulation will be mixed in connection with the administration to the subjects participating in the study. By dispensing the Vacc-4x peptides in water and subsequently mixing the peptides with a Endocine suspension prepared in 15 mM NaOH, a stable formulation lasting for at least 8 hours is achieved.

### Dosage and administration of study drug

Vacc-4x is administered intranasal as a mixture of Vacc-4x peptides and the adjuvant Endocine.

The study includes four groups:

***A low dose group***: 80 µg Vacc-4x (20 µg pr. peptide) divided into two administrations;

40 µg Vacc-4x in 150 µl Endocine for each nostril.

***A medium dose group***: 400 µg Vacc-4x (100 µg pr. peptide) divided into two administrations;

200 µg Vacc-4x in 150 µl Endocine for each nostril.

***A high dose group***: 1200 µg Vacc-4x (300 µg pr. peptide) divided into two administrations;

600 µg Vacc-4x in 150 µl Endocine for each nostril.

***A zero dose group***: Only adjuvant divided into two administrations;

150 µl Endocine for each nostril.

The drug will be administered four times with one week interval; at week 1, week 2, week 3 and week 4.

A DTH test (Vacc-4x 400 µg intra-dermal) will be done at week 8.

### Rationale for dosing regimen

The dose and immunization schedule harmonize with the initial phase of previous studies performed with Vacc-4x (Study CTN B-HIV‑2/2001 and Study CT-BI Vacc-4x 2007/1).

### Subject compliance

Clinical staff at the site is to perform the drug administration. They will record the timing of all administrations in the source notes, which will be transcribed onto the case report forms (CRFs). Ongoing compliance with ART will be supported by the site clinicians according to standard site protocols and will not be formally evaluated in this study.

### Overdose and toxicity management

Following each administration, the subject will be required to remain at the clinic for at least 30 min for observation of any immediate reaction to the administration.

There is no experience with human overdose of Vacc-4x even after systemic (intradermal) injections of high dose. The experience in the nonclinical intravenous studies with mice and rats suggests that even if Vacc-4x is inadvertently delivered to the circulation; clinically important toxicity should not be expected.

## Concurrent medications and Non‑drug therapies

Administration of all concomitant medications must be reported in the appropriate section of the CRF along with dosage information, dates of administration, and reasons for use. Trade names (product names) for concomitant medication should be used, if possible. The total daily dose should be recorded whenever possible. Additionally, diagnostic, therapeutic, or surgical procedures performed during the study period must be recorded in the comments section of the corresponding AE report.

### Permitted medications

Any treatment, which is considered necessary for the subject’s welfare (including supportive care) and which will not interfere with the study drug, may be given at the discretion of the investigator.

### Prohibited medications

Subjects are prohibited from concomitant use of any of the following medications:

- Any other immunomodulating therapy
- Chronic corticosteroids, except for asthma inhalers or topical use
- Other investigational drugs, agents, or devices

## Study drug management

### Packaging of study drug

Vacc-4x will be provided as an investigational drug with the appropriate cautionary statements included on the label per local regulatory requirements.

Endocine will be provided as an investigational adjuvant with the appropriate cautionary statements included on the label per local regulatory requirements.

### Labeling of study drug

The vials of Vacc-4x and with Eurocine (adjuvant) will be labeled with the protocol number, expiration date, batch number, and investigational drug substance delivery address. Additional information will, if needed, be included according to local laws and regulations.

### Preparation of study drug

The preparation of study drug; Vacc-4x and Endocine should be performed by the study site pharmacist (or other responsible person). The date (DD/MM/YYYY) and time (XX: XX [24 hours]) of reconstitution should be recorded. The reconstituted product should be used as soon as possible after preparation. Due to instability of the Vacc-4x peptides, the final vaccine formulation will be mixed in connection with the administration to the subjects participating in the study. The stability of the final vaccine formulation has been tested by physiochemical stability testing of the emulsion. No changes were seen during the 12 hour observation period.

Vacc-4x is to be reconstituted with sterile Water for Injection (without preservative), United States Pharmacopoeia (USP) or European Pharmacopoeia (Eur Pharm).

The dose of Vacc-4 peptide is 80 µg, 400 µg and 1200 µg, respectively. After reconstituting, the peptide solution is mixed with the Endocine adjuvant at a 1+1 ratio and subsequently administered to the subject with 150 ul into each nostril (total 300 ul).

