| Diagnosis and Main Criteria for Inclusion/ Enrollment: | **Inclusion criteria:**   - Age above 18 years, both genders. - HIV positive at least one year. - Clinically stable on ART for the last 6 months (changes in therapy is allowed as long as the viral load is stable). - Documented viral load (HIV-1 RNA) less than 50 copies/mL for the last six months. - Documented stable CD4 cell count ≥ 400x106/L. - Nadir (lowest ever) CD4 cell count ≥ 200x106/L. - Signed informed consent.   **Exclusion criteria:**   - Reported pre-study AIDS-defining illness within the previous year. - Malignant disease. - On chronic treatment with immunosuppressive therapy. - Unacceptable values of the hematologic and clinical chemistry parameters, as judged by the Principle Investigator (or designee), including creatinine values >1.5x upper limit of normal (ULN), and AST (SGOT), ALT (SGPT) and alkaline phosphatase values >2.5x ULN. - Concurrent chronic active infection such as chronic viral hepatitis B or C or active tuberculosis. - Pregnant or breastfeeding women. - Women of childbearing potential not using reliable and adequate contraceptive methods (defined as: use of oral, implanted, injectable, mechanical or barrier products for the prevention of pregnancy; practicing abstinence; sterile) during the study, or sexually active male patients with partners of childbearing potential unwilling to practice effective contraception during the study. - Current participation in other clinical therapeutic studies. - Incapability of compliance to the treatment protocol, in the opinion of the Investigator. | | | |
| Reference Product: | None | | | |
| Treatment Regimen: | During the Treatment Period, all subjects will remain on their ART and receive four immunizations at weeks 1, 2, 3 and 4 with either :  ***A low dose group***: 80 µg Vacc-4x (20 µg pr. peptide) divided into two administrations;  40 µg Vacc-4x in 150 µl Endocine for each nostril.  ***A medium dose group***: 400 µg Vacc-4x (100 µg pr. peptide) divided into two administrations;  200 µg Vacc-4x in 150 µl Endocine for each nostril.  ***A high dose group***: 1200 µg Vacc-4x (300 µg pr. peptide) divided into two administrations;  600 µg Vacc-4x in 150 µl Endocine for each nostril.  ***A zero dose group***: Only adjuvant divided into two administrations;  150 µl Endocine for each nostril. | | | |
| Duration of Participation: | Screening: 1-4 weeks.  Study period: 8 weeks (4 weeks immunization period + 4 weeks follow-up) | | | |

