5. For cryopreservation of PBMC to T cell response assays with optional samples for T cell response kinetics and optional assays on fresh blood samples. X, mandatory assay time points; x, optional time points pending on responsiveness.

During the Treatment Period, all subjects will remain on their ART and receive four immunizations at Weeks 1, 2, 3 and 4, with Vacc‑4x including Endocine as adjuvant.

The study is sequential, meaning that the first five subjects receive either adjuvant only (two patients) or the lowest dose (three patients) 80 µg Vacc-4x together with Endocine (given as 40 µg Vacc-4x as 150µl Endocine solution in each nostril). If the safety evaluation after two weeks is ok, the next dose level will be started, see Figure below:

[figure not shown]

##

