## Procedures for assigning subjects to treatment groups

24 subjects will be randomly enrolled into one of four treatment groups:

***A low dose group***: 80 µg Vacc-4x (20 µg pr. peptide) divided into two administrations;

40 µg Vacc-4x in 150 µl Endocine for each nostril.

***A medium dose group***: 400 µg Vacc-4x (100 µg pr. peptide) divided into two administrations;

200 µg Vacc-4x in 150 µl Endocine for each nostril.

***A high dose group***: 1200 µg Vacc-4x (300 µg pr. peptide) divided into two administrations;

600 µg Vacc-4x in 150 µl Endocine for each nostril.

***A zero dose group***: Only adjuvant divided into two administrations;

150 µl Endocine for each nostril.

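### The stated Endocine volume of 150 µl per nostril conflicts with the 1+1 mixing rule in 6.3.3, and the zero-dose preparation is undefined, so the control may get the same adjuvant as the vaccine arms or twice as much

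*Protocol*

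**What the plan says.** Three places give Endocine as a volume per nostril, and it is the same in every arm. The synopsis (Treatment Regimen) has "40 µg Vacc-4x in 150 µl Endocine for each nostril" for the low dose, section 6.4 has "200 µg Vacc-4x in 150 µl Endocine for each nostril" for the medium dose, and section 6.1.2 has "600 µg Vacc-4x in 150 µl Endocine for each nostril" for the high dose. All three places describe the zero-dose group as "Only adjuvant divided into two administrations", again at 150 µl of Endocine per nostril and with no diluent named.

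Section 6.3.3 sets out the preparation. The peptide is reconstituted in Water for Injection and then "mixed with the Endocine adjuvant at a 1+1 ratio and subsequently administered to the subject with 150 ul into each nostril (total 300 ul"). The section lists the 80, 400 and 1200 µg doses and does not mention the zero dose.

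Three other statements bear on the reading:
- Section 6.1.1 (Vacc-4x): "Vacc-4x should be mixed with Endocine and administered intranasal as a 150µl in each nostril".
- Section 4.1, on the low dose: "given as 40 µg Vacc-4x as 150µl Endocine solution in each nostril".
- Section 6.1.1 (Endocine): the adjuvant "is supplied in vials containing 250 µl of the adjuvant".

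Section 6.3.6 also refers preparation to pharmacy instructions, which are not part of the protocol.

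**The concern.** In the vaccine arms, the dosing sections and the preparation section give different amounts of adjuvant. In the control arm there is a dosing statement but no preparation statement, so the text allows either neat Endocine or Endocine diluted to match the vaccine arms.

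This matters because safety is the primary objective and section 2.7 expects local nasal irritation to be the most common type of adverse event. The Endocine-only arm is the only concurrent evidence of how much irritation occurs without Vacc-4x. Two of the first five subjects, whose safety is reviewed before the next dose level opens (section 4.1), are in that arm. If the control receives more adjuvant than the vaccine arms, it no longer isolates the contribution of the peptides.

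**Working it through.** **Inputs**
- Volume given per nostril: 150 µl, total 300 µl (6.3.3; also 6.1.1 and the flow-chart footnote in 4.1).
- Mixing ratio: 1 part peptide solution to 1 part Endocine (6.3.3), so the Endocine share is 1/(1+1) = 0.5.
- Stated Endocine volume: 150 µl per nostril, all arms (synopsis, 6.1.2, 6.4).
- Nostrils: 2. Immunizations: 4. Endocine vial: 250 µl (6.1.1).

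**The dosing sections read literally**

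150 × 2 = 300 µl Endocine per visit; 300 × 4 = 1200 µl over four visits, in every arm.

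**Vaccine arms under 6.3.3**

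Endocine per nostril = volume given × Endocine share = 150 × 0.5 = 75 µl. Per visit: 75 × 2 = 150 µl. Over four visits: 150 × 4 = 600 µl. This is half the figure in the dosing sections.

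**Can both statements hold?**

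Keeping 150 µl of Endocine and mixing it 1+1 needs 150 µl of peptide solution: 150 + 150 = 300 µl per nostril, and 300 × 2 = 600 µl in total. Section 6.3.3 gives a total of 300 µl. They cannot both hold.

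**Control arm, both readings, against the vaccine arms under 6.3.3**

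| Zero-dose preparation | Per nostril | Per visit | Four visits | Ratio to vaccine arms |
| --- | --- | --- | --- | --- |
| Neat Endocine | 150 µl | 300 µl | 1200 µl | 300/150 = 2.0 |
| Endocine diluted 1+1 | 75 µl | 150 µl | 600 µl | 150/150 = 1.0 |

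Because the volume per nostril is 150 µl either way, a neat control also doubles the Endocine share of what reaches the mucosa: 150/150 = 1.0 against 75/150 = 0.5.

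**Which reading does the text favour?**

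A diluted control dose uses 150/250 = 0.6 of a vial. A neat one uses 300/250 = 1.2 vials and so needs two. The vial size therefore leans towards dilution, as does the use of Endocine solution in 4.1 for a finished preparation. The adjuvant-only wording in 6.1.2, with no diluent, leans towards neat. Neither side is conclusive.

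**The case against.** The strongest reply is that 150 µl Endocine is shorthand for 150 µl of finished product. Sections 4.1, 6.1.1 and 6.3.3 all agree that 150 µl goes into each nostril, and only 6.3.3 describes preparation, so a pharmacist following it would not make up 600 µl. This is plausible and would reconcile the vaccine arms; the 1200 µl figure is then a literal reading of the text, not a likely exposure. It does not settle the control. The same words would mean a half-strength mixture in three arms and something unspecified in the fourth.

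A second reply is that the pharmacy instructions may define the zero dose. They may, and leaving such detail to a manual is common. But section 6.3.6 requires preparation according to the protocol as well, and the protocol's own dosing figures would still conflict with its mixing rule.

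A third reply is that any bias needs two conditions: a neat control, and irritation that rises with adjuvant amount. That stands. The protocol gives no human data on the second condition, and the rat studies in section 2.5 report good nasal tolerance of Endocine, with lesion frequency similar to vehicle in one study. Those data do not exclude a dose effect in humans, but they do not support one.

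Finally, the comparison affected is descriptive, with 6 subjects per arm, and comparisons among the three vaccine doses are untouched. That also stands and limits the weight of the point.

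**Conclusion.** The contradiction is certain: 75 µl against 150 µl of Endocine per nostril in the vaccine arms, a two-fold difference between sections of the same protocol. The imbalance between control and vaccine arms is possible but not established: the ratio is 1.0 if the zero dose is diluted 1+1 and 2.0 if it is neat. With 6.3.3 applied to the vaccine arms and the zero-dose wording taken literally, the result is 2.0.

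If the control is neat, and assuming irritation rises with adjuvant amount, the comparison of nasal tolerability would understate what Vacc-4x adds. If the control is diluted, there is no such bias. No effect on the T-cell or DTH readouts is claimed.

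This should be fixed, because the control in a safety study needs a defined composition. Confidence is medium, since the pharmacy instructions are not available.

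**What to change.** 1. In the synopsis, 6.1.2 and 6.4, describe the vaccine arms as receiving 150 µl of the final 1+1 mixture per nostril.
2. In 6.3.3, add the zero dose: Endocine mixed 1+1 with Water for Injection, 150 µl per nostril. Use the same description for the zero-dose group in the synopsis, 6.1.2 and 6.4. Endocine is then 75 µl per nostril in all four arms. Water for Injection is already the peptide diluent. If a neat control was intended, the protocol should say so and acknowledge the two-fold adjuvant difference.
3. Bring the pharmacy instructions into line.

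Separately, the NaOH concentration is 0.15 M in the synopsis and section 2.5 but 15 mM in 6.1.1, a ten-fold difference (150/15). It applies equally to all arms and plays no part in the imbalance. The supplier should confirm the correct figure and it should be stated once.

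The cost is wording in the protocol and pharmacy instructions, with no extra subjects, visits or procedures.

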### Preparation of DTH-test

DTH skin reactivity testing represents a simple *in vivo* method for monitoring cellular immune responses. The DTH test consists of Vacc-4x with a concentration of 4.0mg/mL. At the pharmacy, a DTH dose is prepared to the final concentration 4.0mg/mL as described in the Pharmacy Manual. A volume of 0.1mL should be drawn into a syringe ready for use. All handling of the product should be in compliance with handling of sterile product for injection. The reconstituted product should be used as soon as possible after preparation, within a maximum of 8 hours. The peptide solution should be stored at 2 to 8oC.

### Storage of study drug

Lyophilized Vacc-4x should be stored at 2 to 8oC within the expiry date printed on the certificate of analysis. Reconstituted Vacc-4x should be stored at 2 to 8oC. Once reconstituted, Vacc-4x is stable for 8 hours.

Endocine adjuvant should be stored at 2 to 8° C. Before mixing with peptide, turn the vial upside down 2-3 times in order to obtain a homogenous emulsion.

### Study drug shipping and handling

Study drugs will be dispatched to a site only after receipt of required documents in accordance with applicable regulatory requirements.

Study drug must be prepared, dispensed and administered according to procedures described herein and in the pharmacy instructions for the study. Only subjects enrolled in the study may receive study drug, in accordance with all applicable regulatory requirements. Only authorized site staff may supply or administer study drug. All study drugs must be stored in a secure area with access limited to the Investigator and authorized site staff and under physical conditions that are consistent with study drug specific requirements.

### Study drug accountability

The pharmacy (or other qualified designee) is responsible for maintaining accurate records of Vacc-4x shipments (receipts) and for recording the use of Vacc-4x on accountability forms. The pharmacy is also responsible for the dispensation and return of the Vacc-4x. Any Vacc‑4x accidentally or deliberately destroyed must be accounted.

Partially used vials must be accounted before they are destroyed at the study center according to local procedures.

Unused vials must be destroyed locally or returned to the investigational drug substance suppliers. At the finalization of the clinical study, the overall numbers of Vacc-4x vials shipped to the study centre and the number destroyed and/or returned must be provided by the pharmacy. An account must be given of any discrepancies that might have occurred during the study.

The pharmacy (or other qualified designee) is responsible for maintaining accurate records of Endocine shipments (receipts) and for recording the use of Endocine on accountability forms.

## Procedures for assigning subjects to treatment groups

24 subjects will be randomly enrolled into one of four treatment groups:

***A low dose group***: 80 µg Vacc-4x (20 µg pr. peptide) divided into two administrations;

40 µg Vacc-4x in 150 µl Endocine for each nostril.

***A medium dose group***: 400 µg Vacc-4x (100 µg pr. peptide) divided into two administrations;

200 µg Vacc-4x in 150 µl Endocine for each nostril.

***A high dose group***: 1200 µg Vacc-4x (300 µg pr. peptide) divided into two administrations;

600 µg Vacc-4x in 150 µl Endocine for each nostril.

***A zero dose group***: Only adjuvant divided into two administrations;

150 µl Endocine for each nostril.

# Study Procedures

## Time and events schedule

The study procedures to be conducted for each subject are divided into the following study phases: Screening (up to 4 weeks), Treatment Period (4 weeks), Follow-up Period (4 weeks).

The procedures to be completed during each of these phases are presented in the Study Flow Chart (Section 4.1, Table 2). Detailed descriptions of the assessments and the definition of study endpoints are provided in Section 8 (Study Assessments and Measurements). Any deviation from study procedures should be noted in the source documents and significant deviations should be reported to the Investigational drug substance suppliers immediately.

## Subject informed consent

Prior to performing any study procedures, the investigator (or his/her designated staff) will obtain written informed consent from the subject as described in Section 12.6.1. After reading the informed consent document and having all questions answered, the subject must give consent in writing. The subject's consent must be confirmed at the time of the subject’s signature by the personally dated signature of the person conducting the informed consent discussions. A copy of the signed consent document must be given to the subject or the subject's legally authorized representative. “Legally authorized representative” means an individual or judicial or other body authorized under applicable law to consent on behalf of a prospective subject to the subject’s participation in the procedure(s) involved in the research. The investigator will retain the original signed consent document. The investigator will not undertake any measures specifically required for the clinical study until valid consent has been obtained.

